## Introduction

Severe symptomatic aortic stenosis is a heart condition which affects one-in-ten people over the age of 75 (1). Surgical aortic valve replacement was traditionally the usual treatment for this condition, yet approximately one third of patients are unsuitable for surgery due to older age or comorbidities (2). In 2002, transcatheter aortic valve implantation (TAVI) was introduced as a non-surgical alternative for the treatment of severe symptomatic aortic stenosis and has since become the standard of care in the large number of patients with prohibitive surgical risk (3). Recommendation for TAVI treatment has been extended to low-risk patients in recent years (4, 5). During a TAVI procedure, a new valve is positioned into the heart from a blood vessel in the groin or an anterograde transapical approach, thus circumnavigating the need for cardiopulmonary bypass and sternotomy (6).

While TAVI is associated with positive post-procedural outcomes, such as lower mortality and improvements in quality of life (7–9), cognitive complications including delirium and cognitive decline are common (10, 11). Delirium is an acute and fluctuating disorder of deficits in attention and arousal (12). A previous meta-analysis by our group found that one-in-four TAVI patients experience delirium in the days following their procedure (10). In older individuals delirium is associated with a range of poor outcomes including functional decline, loss of independence, cognitive decline and dementia, institutionalization and death (13, 14). Furthermore, another meta-analysis by our group demonstrated that cognitive decline is seen in up to 14% of patients in the year following TAVI (11). Cognitive decline can lead to clinically significant cognitive impairments including mild cognitive impairment (MCI) and dementia (15, 16).

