### Sample Size

We want to capture any relationships between risk factors and cognitive outcomes which have potential clinical utility. As such, to detect a medium-large effect size or higher (*r* ≥ 0.4), with power = 0.8, α = 0.05, we computed [using G^*^Power statistical analysis software (54)] that a sample size of 44 is required. To account for attrition, a total of 60 participants will be recruited.

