##### Additional Secondary Outcomes

Secondary outcomes also comprise quality of life and activities of daily living, which are measured using the EuroQol-5D (63) and Barthel Index of Activities of Daily Living (64), respectively, at 3-, 6-, and 12-months after TAVI. Mortality was also recorded as a secondary outcome at the same three timepoints post-procedure.

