**Additional Measures**							
Saliva sample (APOE4 allele)	5	X					
**Medical History**	NA^*†*^						
Renal disease		X					
Previous stroke/TIA		X					
Atrial fibrillation		X					
Coronary artery disease		X					
Hypertension		X					
Peripheral vascular disease		X					
**Risk Scores**	NA^*†*^						
EuroSCORE II		X					
Society of Thoracic Surgery		X					
**Procedural Factors**	NA^*†*^						
Valve access type			X				
Procedure time			X				
**Population Characteristics**	NA						
Age		X					
Gender		X					
Height		X					
Weight		X					
Body mass index		X					
**Population Characteristics (collected at baseline)**	5						
Waist circumference		X					
Years in education		X					
Social engagement		X					
Physical activity		X					
**Approximate session durations (minutes)**		120	20	20	45	45	45

*CANTAB, Cambridge Neuropsychological Test Automated Battery; D1, day 1 post-TAVI; D2, day 2 post-TAVI; 3 M, 3-months post-TAVI; 6 M, 6-months post-TAVI; 12 M, 12-months post-TAVI; NA, Not applicable; TIA, transient ischemic attack*.

* *This assessment has parallel versions (or randomized aspects) to be used in follow-up sessions*.

† *Assessments are conducted/collected by the Royal Adelaide Hospital (administration, nursing staff and doctors) in the lead up to TAVI and during hospital stay, all other assessments to be conducted by researcher*.

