### Data Analysis

To determine the relationship between the potential risk factors measured within this study and outcomes (primary and secondary), a series of univariate logistic and linear regressions will be conducted. Each predictor will be entered into a separate model for each primary outcome: presence vs. absence of delirium post-TAVI, as well as presence vs. absence or cognitive decline. The same will be done for secondary outcomes: cognition, mortality, quality of life, and activities of daily living at each follow-up (3-, 6-, and 12-months post-TAVI). Logistic regressions will be run for categorical outcomes (cognitive decline, delirium, and mortality) and linear regressions will be run for continuous outcomes (cognition, quality of life, activities of daily living). As this is an exploratory, effect-finding study, we will not correct for multiple comparisons and multivariable models will not be run. The purpose of this study is to propose variables to be taken forward into independent and larger samples, to develop TAVI-specific risk prediction tools for delirium and cognitive decline.

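### Logistic regressions are planned on about 6 to 15 events per primary outcome, so some binary-predictor models will separate unless a penalised fit is named

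*Protocol article*

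**What the plan says.** The Data Analysis section of the protocol article enters each predictor into its own model, without multivariable models or multiplicity correction. For the binary outcomes: "Logistic regressions will be run for categorical outcomes (cognitive decline, delirium, and mortality". Mortality is modelled at 3, 6 and 12 months, in line with the Additional Secondary Outcomes section: "Mortality was also recorded as a secondary outcome at the same three timepoints post-procedure". No estimator, test or interval method is named. Penalised regression appears only in the Discussion, as advice for future multivariable models.

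The event counts follow from two sections. The Introduction gives the rates: "one-in-four TAVI patients experience delirium in the days following their procedure" and "cognitive decline is seen in up to 14% of patients in the year following TAVI". The Sample Size section gives the numbers: "a sample size of 44 is required" and "To account for attrition, a total of 60 participants will be recruited".

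Table 2 and the measure descriptions contain at least nine predictors that are binary or likely to be analysed as such: six medical-history items (for example "Peripheral vascular disease"), valve access type, diplopia and APOE4.

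**The concern.** With a binary predictor and a binary outcome, a one-predictor logistic model is a 2×2 table. If one cell is empty, the maximum-likelihood odds ratio is zero or infinite, its standard error explodes and the Wald p-value goes towards 1. Few events make empty cells likely. So does a strong association, because the events then gather in one group.

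The study exists to choose variables for later prediction models. If an important predictor produces a failed fit or a Wald p-value near 1, the screening step can pass over the variable it was meant to find. Three mortality models add little, because a death by 3 months is counted again at 6 and 12 months.

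**Working it through.** **The plan's own figure.** The Sample Size section aims "to detect a medium-large effect size or higher (*r* ≥ 0.4), with power = 0.8, α = 0.05". For a two-sided test in a single-predictor linear model, the noncentrality is √N·r/√(1−r²) = √44 × 0.4/√0.84 = 2.895 on 42 degrees of freedom. This gives power 0.807 at N = 44 and 0.798 at N = 43, so 44 reproduces. It rests on a correlation, not on a logistic model with these event rates.

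**Expected events.**
- Delirium: 0.25 × 60 = 15; 0.25 × 44 = 11.
- Decline: 0.14 × 60 = 8.4; 0.14 × 44 = 6.2.
- Deaths: no rate is given.

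**Chance of an empty cell with no association.** With m of N exposed and event probability p, a group has events and non-events both present with probability 1 − (1−p)^m − p^m. The chance of an empty cell is one minus the product of this term over the two groups. It is then averaged over m ~ Binomial(N, exposure prevalence).

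Hand check for decline with 22 exposed and 22 unexposed: 0.86^22 = 0.036, so 1 − (1 − 0.036)² = 0.071. Averaging over m gives 0.081.

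| Outcome | 10% exposed | 20% | 30% | 50% |
|---|---|---|---|---|
| Delirium, 25%, N = 60 | 23% | 4.6% | 0.9% | 0.07% |
| Delirium, 25%, N = 44 | 35% | 10.5% | 3.3% | 0.6% |
| Decline, 14%, N = 60 | 43% | 18% | 7.8% | 2.6% |
| Decline, 14%, N = 44 | 55% | 29% | 16% | 8% |

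For mortality at N = 60 and exposure 20–50%, the chance is 80–87% at an assumed 2% death rate, 39–59% at 5%, 9–30% at 10% and 2–16% at 15%. The chance of no deaths at all is 0.98^60 = 30% at 2% and 0.95^60 = 5% at 5%.

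**Expected number of separated models.** Take ten binary predictors (the nine above plus gender) with assumed prevalences of 20–50%. About 0.2–0.4 of 10 delirium models and 2.7–5.2 of 30 decline models (three timepoints, 14% at each) would separate, over N = 60 to 44.

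**A real effect.** Take decline at N = 44, 14% overall, half exposed and a three-fold risk. Then p₀ = 0.14/(0.5 + 0.5 × 3) = 0.07 and p₁ = 0.21. With 22 per group, the chance of an empty cell is about 1 − (1 − 0.93^22)(1 − 0.79^22) = 1 − 0.797 × 0.994 = 0.21. Averaged over m it is 21.5%, about 22%. Summing over all tables, and counting an empty cell as not significant for Wald:

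| Test at 5% | Size, no association | Power, three-fold risk |
|---|---|---|
| Wald | 1% | 7% |
| Likelihood ratio, unpenalised | 7% | 30% |
| Firth, profile penalised likelihood | 4% | 23% |

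**The extreme table.** Suppose all six events fall among 22 exposed and none among 22 unexposed. A standard fit returns log-OR 22.6, SE 16,941 and Wald p = 0.999, although Fisher's exact p is 0.02 and the likelihood-ratio p is 0.002. For a 2×2 table, Firth equals adding 0.5 to each cell: OR = (6.5 × 22.5)/(16.5 × 0.5) = 17.7. Its test statistic is 2{6.5 ln(6.5/23) + 16.5 ln(16.5/23) + 0.5 ln(0.5/23) + 22.5 ln(22.5/23) − 7 ln(7/46) − 39 ln(39/46)} = 7.03, p = 0.008.

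**What Firth does not do.** For 0/9 against 6/35 it gives OR = (0.5 × 29.5)/(9.5 × 6.5) = 0.24, with a Wald interval on the augmented table of 0.01 to 4.6. The estimate is finite, but little has been learned.

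**The case against.** The strongest reply is that the article says only that logistic regressions will be run. Firth or exact estimation fits that sentence, sparse-data handling is often left to an analysis plan, and that plan is not shown. A reader might infer that maximum likelihood with Wald tests is laid down, or that predictors will be dropped on Wald p-values. The text states neither. What remains is that the article does fix the model family for outcomes with few events, and the unqualified term usually means maximum likelihood. A better choice can be named in the same sentence.

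A reader might also infer that many or most models will separate. The figures do not support this for the primary outcomes. Delirium models seldom separate unless the predictor is present in, or absent from, about 10% or fewer of patients, and at 20–50% exposure 71–97% of decline models do not. Many predictors are continuous or scale scores and are less exposed. The largest percentages belong to mortality, a secondary outcome whose rate is assumed here.

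The decline count is also on the low side. The Cognitive Decline section chose the 4-point cut-off to lean towards false positives, so the rate may exceed 14%. At an assumed 20% with N = 44 and half exposed, separation with no association falls to 1.9%. Wald power for a three-fold risk is then 22%, against 40% for the likelihood-ratio test.

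Finally, part of the gap between tests is Wald conservatism rather than separation, and the unpenalised likelihood-ratio test is somewhat too liberal. The Firth comparison largely meets this point, since its size is about 4%. Power remains low throughout, and that is a limit of the sample size.

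**Conclusion.** The concern holds in a limited form. On the article's own figures the primary binary outcomes have roughly 11–15 and 6–8 events. Under standard maximum likelihood, some binary-predictor models will give infinite odds ratios and uninformative Wald p-values. The risk is material for decline, small for delirium except with uncommon predictors, and undetermined for mortality until a death rate is known.

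The gain from a penalised fit is clearest where the study most needs it, with strong predictors of decline. These sizes rest on assumed exposure prevalences, on 14% applying at each follow-up, and on N between 44 and 60.

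A reader might infer that death by a fixed timepoint is an invalid endpoint and that a Cox model is required. The documents do not support that. The endpoint is valid, and the article does not say that dates of death are collected.

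**What to change.** In the Data Analysis section, state that every binary-outcome model will be fitted by Firth penalised logistic regression, with profile-penalised-likelihood confidence intervals and tests. Report 3- and 6-month mortality descriptively and model mortality once, at 12 months. A Cox model is optional, and only if dates of death are available.

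The cost is a sentence or two and standard software, with no extra participants or assessments. The downside is that odds ratios are shrunk slightly towards 1. Intervals remain wide, because penalisation adds no information.

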## Discussion

Risk prediction tools which accurately identify those at increased risk for post-procedural cognitive decline and delirium are enormously valuable. Early identification allows for timely diagnosis of these negative outcomes, which is crucial for their effective management. Additionally, pre-procedural risk identification is essential for the successful implementation of preventative programs or other multicomponent intervention (17). A meta-analysis has shown that the use of such multicomponent interventions, such as the hospital elder life program (71), can lead to a significant reduction in delirium incidence (OR = 0.47) (72). In order to develop such accurate and useful risk prediction tools for post-TAVI cognitive decline and delirium, we first must understand what factors to include. We are going to take a broad, inclusive and clinically relevant approach to take a step in this direction. However, our conclusions must be balanced against the limitations of our sample which has a bias toward individuals living in metropolitan South Australia (due to follow-up procedure logistics) and with a lower socio-economic status, only recruited from one public hospital. This is an effect-finding study using single-predictor regression models. As suggested by Lindroth et al. (73), future studies using multiple variables to develop a prediction model should consider utilizing lasso regression (or a similar penalized regression approach) in order to avoid overfitting. There has been limited and conflicting research investigating the utility of frailty measures in the prediction of delirium following TAVI (41–43), and even less research for cognitive decline. Measures of frailty are broad and vary greatly in the factors they encompass. We propose that by investigating individual factors drawn from frailty and aging literature, we can identify those with the best predictive utility. Future research can then implement these measures into new risk prediction models for TAVI, which can then be tested in larger samples.

## Ethics Statement

The studies involving human participants were reviewed and approved by the Central Adelaide Local Health Network (CALHN) Human Research Ethics Committee (Reference number: R20170916) and the University of South Australia Human Ethics Committee (Reference number: 200830). The patients/participants provided their written informed consent to participate in this study.

## Abbreviations

ACE-III: Addenbrooke's Cognitive Examination III
APOE4: Apolipoprotein E4
BCVA: Best Corrected Visual Acuity
CAM: Confusion Assessment Method
CANTAB: Cambridge Neuropsychological Test Automated Battery
EuroSCORE: European System for Cardiac Operative Risk Evaluation
GDS: Geriatric Depression Scale
ICU: Intensive Care Unit
MCI: Mild Cognitive Impairment
MDAS: Memorial Delirium Assessment Scale
MOT: Motor Orientation Task
NPI-Q: Neuropsychiatric Inventory Questionnaire
PRM: Pattern Recognition Memory
RTI: Reaction Time
STS: Society of Thoracic Surgery
TAVI: Transcatheter Aortic Valve Implantation.
